#### Main trial

The sample size control group rate of 16% is based on GlobalSurg 2 feasibility data [19]. To detect an absolute difference of 4% (relative reduction of 25%) to 12%, with 90% power and using a 5% two-sided significance level, it requires 1580 participants in each group. To allow for clustering of centres the sample size was adjusted by inflating the estimate by the design effect given by 1 + (*n*–1)*ρ*, where *n* is the average cluster size and *ρ* is the estimated intra-class correlation coefficient. The intra-class correlation coefficient calculated from GlobalSurg 2 feasibility data was 0.02 [20]. We expect this to be lower in ChEETAh; there are a smaller number of centres within a limited number of countries where there is willingness to participate in a clinical trial, hence less variation is likely. With an assumption of an intra-class correlation coefficient value of 0.01, power calculations indicated that we need 30 clusters per treatment group with an average of 170 participants per cluster. After allowing for 15% loss to follow-up rate for participants and 5% drop out rate for clusters, the total sample size is 6400 per group (32 clusters per group with an average of 200 participants). This sample size also allows the cluster size to vary (coefficient of variation = 0.5). The sample size was calculated using the clustersampsi Command in Stata 15 (StataCorp LLC, TX, USA).

### Recruitment {15}

Site opening and trial recruitment will be monitored during the internal pilot phase. The ability of the CHEETAH trial delivery network’s to recruit to time and target has been demonstrated in the FALCON trial: a pragmatic multi-centre factorial randomised controlled trial testing measures to reduce surgical site infection in low- and middle-income countries [21]. This study recruited 5789 patients 12-months ahead of schedule even during the SARS-CoV-2 pandemic, demonstrating the resilience and flexibility of our research network. We will maintain flexibility to increase the number of sites or countries to reach the desired sample size if unforeseen challenges to recruitment arise, so long as the country eligibility criteria (e.g. at least 4 participating sites per country) are maintained.

### Assignment of interventions: allocation

#### Sequence generation {16a}

Clusters (hospitals) will be randomly allocated (1:1) to change of gloves and instruments (intervention group) or current routine hospital practice. Randomisation will be minimised by country (minimum participation of four clusters per country in order to achieve balance by treatment arm) and hospital type (referral hospital [yes or no]—a referral hospital is defined as a hospital that accepts pre-operative referrals from other surgical teams).

#### Concealment mechanism {16b}

Randomisation will occur centrally, and participating theatres will be confirmed in each participating centre before randomisation is performed. Hospitals will be informed of their random allocation before any patients are assessed for eligibility.

#### Implementation {16c}

The allocation sequence will be generated by the CHEETAH Trial Statistician and the site informed by the Senior Trial Manager. Selection bias will be carefully monitored by the Trial Management Group (TMG). The TMG includes those individuals responsible for the day-to-day management of the trial and will include the trial chief investigator, lead methodologists, patient representatives, and ChEETAh trial management staff from the International Coordinating Centre (ICC)/Birmingham Clinical Trials Unit (BCTU). Assessment of selection bias will primarily consist of monitoring of baseline characteristics by trial arm and by country. The aim of this will be to check for any indication that patients may have been recruited selectively (i.e. unusual or unexplained imbalance in any particular subset of patients).

In addition, during on-site visits, the ICC/BCTU will monitor Hubs, and Hubs will monitor Spokes, to confirm all eligible patients have been entered into ChEETAh by reviewing the ChEETAh register against the hospital’s standard theatre logbook. The ChEETAh register will be completed by a member of the ChEETAh research team at the hospital and is a list of all patients (compiled from the standard hospital theatre logbook). We will monitor for selection biases between arms by measuring intended and actual theatre opening plans and daily registers to confirm that all eligible patients are included.

### Assignment of interventions: blinding

#### Who will be blinded {17a}

The primary outcome of SSI will be determined by a computer-based algorithm and defined according to the CDC criteria.

Outcome assessor(s) will be trained to ask a series of specific questions relating to the definition of SSI and to record the responses provided by the patient. As this is a cluster randomised trial and outcome assessors are likely to know the hospital allocation they are unlikely to be blinded. Assessors will receive formal training in the outcome of wounds, and the computer-based algorithm will determine whether the primary outcome has been met according to the CDC criteria.

The patient will however be blinded to the treatment allocation as patients will not be aware of the cluster (hospital) randomisation and are not aware of the detailed specifics around the operation, as with any operation.

#### Procedure for unblinding if needed {17b}

As the CHEETAH intervention is a one-off in-theatre change of sterile gloves and instruments with no materials left in situ nor change to post-operative care, we do not anticipate a need to emergency unblind patients. Patients can request to be unblinded upon request after completion of the trial primary analysis.

### Data collection and management

#### Plans for assessment and collection of outcomes {18a}

Patients will be reviewed, at the time of discharge from hospital, and at post-operative day 30. All patients who have been registered and operated on regardless of adherence to the randomised hospital allocation should be followed up.

The primary outcome will be captured from the time of the index surgery until postoperative day 30. Once registered into the CHEETAH trial, the patient will be contacted on or after, but as close as possible to post-operative day 30 by a member of the research team (from the Hub or Spoke) to complete the 30-day follow-up assessment. If a patient achieves the primary outcome before 30 days, they should still be assessed at 30 days to record secondary outcome measures.

Follow-up will be completed in-person for those returning to hospital as part of standard, routine care; all other patients will be followed up by telephone 30-days post-surgery.

For patients being followed-up by telephone, they will be required to answer questions from a standardised script of questions to assess for SSI (see Appendix 6). Within the GlobalSurg-2 cohort study, 43.1% (6907/16015) of patients were approached for telephone assessment, providing initial feasibility evidence for this approach [22]. Validity of telephone wound follow-up after hospital discharge has been demonstrated in several high-quality studies. In the UK, the Bluebelle trial used telephone-based SSI follow-up for primary outcome assessment with high sensitivity and specificity [23]. A study from the USA demonstrated equivalent rates of SSI between groups undergoing telephone follow-up and in-person assessment after caesarean section [24]. In LMICs, a pre- and post-implementation study of SSI reduction measures across four sub-Saharan African countries published in *Lancet Infectious Disease* successfully used telephone follow-up of the primary outcome measure (SSI according to CDC criteria) [25]. Validation studies in Tanzania and Kenya have also demonstrated accuracy of telephone surveillance for postoperative SSI [26, 27]. Over 80% of the population of LMICs have access to a mobile telephone justifying the use of an efficient, telephone-based follow-up pathway in CHEETAH [28, 29].

In CHEETAH, a member of the site research team will contact the patient and ask the questions from the follow-up form. In the case of children, a member of the site research team will contact the parent/guardian and ask the questions from the follow-up form. SSI will be determined by a computer-based algorithm and defined according to the CDC criteria. Outcome assessor(s) will be trained to ask a series of specific questions and to record the responses provided by the patient. The algorithm will determine whether the primary outcome has been met, overcoming the subjective interpretation of CDC criteria, which has potential to introduce bias.

Other questions, as indicated, will be completed from a review of the patient notes during admission, checking hospital records (electronic or paper), discharge summaries and handover lists for re-attendances or re-admissions and checking for emergency department re-attendances.

#### Plans to promote participant retention and complete follow-up {18b}

Trial retention will be actively monitored at a site level by the ITMG. Top tips for optimising telephone follow-up and retention within global randomised trials in surgery have been co-produced between trial site investigators, research coordinators, and community engagement and involvement representatives from LMICs and will be implemented to support sites with < 95% completion of follow-up for eligible patients.

#### Data management {19}

Trial data are recorded in a variety of ways, via completion of the CHEETAH Operation Sticker (Appendix 7), CHEETAH Register, on CRFs, and then entered on to a secure online REDCap server hosted by the University of Birmingham. Data are collected intra-operatively, at trial entry, at discharge from hospital and at 30-days post-surgery (see Table 1). Source data are generally kept as part of the participants` medical notes generated and maintained at site; however, in the CHEETAH trial, the completed 30-day follow-up form will be source data. Data reported within the CRF booklet will be consistent with the source data and any discrepancies will be explained. All missing and ambiguous data will be queried. Staff delegated to complete CRFs will be trained to adhere to the requirements of data capture as explained in the ChEETAh training slides. In all cases, it remains the responsibility of the site’s local principal investigator to ensure that the CRF has been completed correctly and that the data are accurate. This will be evidenced by the signature of the site’s principal investigator, or delegate(s), on the CRF.

#### Confidentiality {27}

Data will be pseudonymised on the REDCap server (https://bctu-redcap.bham.ac.uk/) with only a unique trial number used to identify each patient, before being transferred from the site to the University of Birmingham for analysis. The security of the Trial Database System is governed by the policies of the University of Birmingham. Data management and data security within BCTU will abide by the requirements of the General Data Protection Regulations (GDPR) and any subsequent amendments. The final dataset will be stored for 25 years in accordance with UK rules.

#### Plans for collection, laboratory evaluation, and storage of biological specimens for genetic or molecular analysis in this trial/future use {33}

There will be no biological specimens collected.

## Statistical methods

### Statistical methods for primary and secondary outcomes {20a}

#### Internal pilot

Percentages of subjects that adhered to allocation and subjects that were followed up will be presented alongside 95% confidence intervals. The percentages will be presented for all centres combined and for each centre separately.

#### Main trial

A separate Statistical Analysis Plan will be produced and will provide a more comprehensive description of the planned analysis. A brief outline of the analysis is given below. All analysis will be based on the intention to treat principle, i.e. participants from all hospitals will be analysed in the groups to which the hospitals were allocated. Summary statistics will be presented for all outcome measures, with the relevant adjusted effect measures, 95% confidence intervals and *p*-values from two-sided tests. The effect of intervention will be adjusted for country and hospital type (district versus referral hospital). For all binary outcomes, adjusted relative risks (with 95% confidence intervals) will be calculated using log binomial regression models. The adjusted model will include country and hospital type as fixed effects and centre as a random effect to account for the clustered nature of the sample. If the log-binomial model fails to converge, a Poisson regression model with robust standard errors will be used to estimate the same parameters. If this also fails to converge, unadjusted estimates will be produced from the log-binomial model taking account the cluster design. It will be made clear in the final report why this occurred (e.g. not possible due to low event rate/lack of model convergence). For all time to event outcomes, Cox-proportional hazards models will be used, if the assumptions of proportionally are met, and adjusted hazard ratios with 95% confidence intervals presented. A log-rank test will be used to assess statistical significance. The primary analysis for the study will occur once all participants have completed the 30-day follow-up assessment, corresponding outcome data has been entered onto the study database, and it has been validated ready for analysis. We will conduct sensitivity analysis on imbalanced factors between trial arms, which are expected in a cluster randomised design.

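### The log-rank test named for time-to-event outcomes ignores hospital clustering, so p-values for the secondary outcomes analysed this way would be too small

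*Protocol article*

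**What the plan says.** The unit of allocation is the hospital: "Clusters (hospitals) will be randomly allocated (1:1) to change of gloves and instruments (intervention group) or current routine hospital practice" (Sequence generation {16a}). Allocation is minimised by country and by whether the hospital takes referrals.

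The Main trial text under Statistical methods {20a} describes two analyses.

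- **Binary outcomes:** a log-binomial model with country and hospital type as fixed effects and "centre as a random effect to account for the clustered nature of the sample". Even the last fallback, an unadjusted estimate, is to respect the cluster design.
- **Time-to-event outcomes:** "For all time to event outcomes, Cox-proportional hazards models will be used, if the assumptions of proportionally are met, and adjusted hazard ratios" with confidence intervals. The next sentence reads "A log-rank test will be used to assess statistical significance". No stratified, clustered or robust form of the test is named.

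The same section says that the intervention effect will be adjusted for country and hospital type, and that p-values will accompany adjusted effect measures. The sample size section allows for clustering as well: "To allow for clustering of centres the sample size was adjusted by inflating the estimate by the design effect". Adverse event reporting and harms {22} gives the cluster design as a reason why crude differences in death rates need adjustment.

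**The concern.** An ordinary log-rank test computes its variance as if patients were independent. Here every patient in a hospital has the same allocation, so any real difference between hospitals adds variance to the treatment comparison that the test does not count. The test statistic is then too large on average and the p-value too small. The error always runs towards false positives.

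The sentence also separates the p-value from the estimate. The hazard ratio is to be adjusted, whereas the log-rank test corresponds to an unadjusted comparison of the arms. A report could show a log-rank p-value below 0.05 beside a clustered, adjusted confidence interval that includes 1, with no rule for which one counts.

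At stake is a false claim of benefit or harm on a secondary outcome. The primary outcome is binary and its model carries a centre effect.

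**Working it through.** **Inputs from Sample size {14}, Main trial**

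- Control rate: "The sample size control group rate of 16% is based on GlobalSurg 2 feasibility data"; intervention rate 12%.
- Unclustered size: "with 90% power and using a 5% two-sided significance level, it requires 1580 participants in each group".
- ICC for surgical site infection: 0.01 assumed for planning, 0.02 calculated from the feasibility data.
- 30 hospitals per arm with an average of 170 patients, coefficient of variation (CV) of cluster size 0.5. After losses, 32 hospitals per arm with 200 patients each.

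**Input not in the document**

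- The ICC of any time-to-event outcome. The infection values are borrowed, and a range is shown.

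**Step 1: reproduce the plan's own figures.** The two-proportion formula for 16% against 12%, 90% power and two-sided 5% gives 1580 per arm, as stated. With unequal clusters the design effect is

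DE = 1 + [(1 + CV²)m − 1] × ICC.

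At m = 170, CV = 0.5 and ICC = 0.01: (1.25 × 170) − 1 = 211.5, so DE = 1 + 2.115 = 3.115. Then 1580 × 3.115 ≈ 4922 per arm, or 4922/170 = 28.95 hospitals. With 30 hospitals of 170 the power is 0.910 (normal) or 0.901 (t, 58 df). Losses: 30/0.95 = 31.6, rounded up to 32; 170/0.85 = 200; 32 × 200 = 6400. The plan's sample size therefore reproduces, and it relies on a design effect of about 3.

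**Step 2: type I error if the design effect is ignored.** The naive statistic has variance DE instead of 1 under the null, so

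type I error = 2 × [1 − Φ(1.96/√DE)].

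At m = 170 and CV = 0.5:

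| ICC | DE | 1.96/√DE | Type I error |
|---|---|---|---|
| 0.001 | 1.212 | 1.78 | 7.5% |
| 0.005 | 2.058 | 1.37 | 17.2% |
| 0.01 | 3.115 | 1.11 | 26.7% |
| 0.02 | 5.230 | 0.86 | 39.1% |
| 0.05 | 11.575 | 0.58 | 56.5% |

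**Step 3: sensitivity to cluster size.** For ICC 0.01 and 0.02, equal clusters of 170 give 23.2% and 34.9%. Clusters averaging 200 with CV 0.5 give 29.4% and 42.3%.

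**Step 4: check on the log-rank test itself.** An ordinary log-rank test was simulated with no true effect, 30 hospitals per arm, mean size 170, CV 0.5, censoring at 30 days, and 30-day event proportions of 5%, 14% and 80% (1500 runs per setting). Rejection rates were 8–9% at ICC 0.001, 25–30% at 0.01 and 39–42% at 0.02, in line with the formula.

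**Step 5: effect of minimisation.** Balancing country and hospital type removes part of the between-hospital variation from the comparison. The document does not say how much. If half of an ICC of 0.01 were removed (an assumption), the 0.005 row applies and the error is about 17%.

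**Step 6: would stratifying rescue the test?** Stratifying by hospital would not, because allocation is constant within a hospital and each stratum carries no treatment contrast. Stratifying by country and hospital type would still ignore variation between hospitals of the same type in the same country.

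**The case against.** The strongest reply is that the article calls its analysis text a brief outline and defers to a separate analysis plan, and that its general statements on adjustment show that clustering was understood. This disposes of one complaint a reader might add, namely that the Cox sentence names no centre term. That detail can be left to the analysis plan and is not held against the protocol. It does not dispose of the log-rank sentence, which names a specific test. An analysis plan that follows the sentence inherits the fault, and one that corrects it departs from the protocol.

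Four stronger readings are tempting, and the document does not support them.

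- **That the false-positive rate would be 27% to 39% as a matter of fact.** The ICCs behind those figures are for surgical site infection. None is given for a time-to-event outcome, cluster size matters, and minimisation works in the other direction.
- **That length of stay and return to normal activities are both affected and depend strongly on hospital practice.** Outcomes {12} labels nothing as time-to-event. Return to activities and death are worded as events within 30 days, which is binary in form, and patients are reviewed only at discharge and at day 30. Length of stay is the clearest candidate. The document says nothing about how strongly it varies by hospital.
- **That early stopping is compromised.** The data monitoring text speaks of major outcomes without saying which they are or how they would be tested.
- **That the main conclusion is at risk.** The primary outcome has a centre random effect, and the sample size is unaffected.

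**Conclusion.** The concern holds in limited form. The protocol fixes a significance test that is invalid under its own randomisation scheme and conflicts with its own statements on adjustment and clustering. The direction is certain for any positive ICC left after minimisation: p-values are too small.

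The size is conditional: about 27% to 39% in place of 5% if time-to-event outcomes cluster as infection does, at 170 per hospital and CV 0.5. Over ICCs of 0.001 to 0.05 it runs from 7.5% to 56%, before any reduction through minimisation.

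This should be corrected before analysis. Because it is confined to secondary time-to-event outcomes that the article does not list by name, it ranks below a defect that would threaten the trial's main result.

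**What to change.** Replace the log-rank sentence. State that, for each time-to-event outcome, the p-value and the 95% confidence interval both come from one Cox model adjusted for country and hospital type, with either a shared frailty for centre or a cluster-robust variance with a small-sample correction. A cluster-adjusted log-rank test may be kept as an unadjusted check. It would also help to name the outcomes to which the sentence applies.

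The cost is one sentence and no new data. Intervals widen and p-values rise for these outcomes. On the same assumptions the standard error grows by √3.115 ≈ 1.8 at ICC 0.01 and √5.23 ≈ 2.3 at ICC 0.02, relative to an analysis that ignores clustering. The lost precision was never real.

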### Interim analyses {21b}

Interim analyses of efficacy for presentation to the independent DMC will take place during the study. The committee will meet prior to study commencement to agree the manner and timing of such analyses but this is likely to include the analysis of the primary and major secondary outcomes at annual intervals. Criteria for stopping or modifying the study based on this information will be ratified by the DMC. Details of the agreed plan will be written into the Statistical Analysis Plan. An interim, blinded publication of the pilot study will be considered by the Trial Steering Committee to report early strategies in randomisation and allocation. By presenting these data as blinded to allocation, they can remain in the main phase analysis, and if necessary, combined event rates will be presented to prevent unblinding. Secondary publications of data will be considered by the Trial Steering Committee.

### Methods for additional analyses (e.g. subgroup analyses) {20b}

Tests for statistical heterogeneity (e.g. by including the treatment group by subgroup interaction parameter in the regression model) will be performed prior to any examination of effect estimate within subgroups. The results of subgroup analyses will be treated with caution and will be used for the purposes of hypothesis generation only. The planned subgroup analyses include country and region (West Africa, Southern Africa, India and Mexico), type of hospital (e.g. elective versus emergency), contamination of wound (e.g. clean-contamination versus contaminated/dirty), type of hospital (district versus referral), and children versus adults. We will also perform a subgroup analysis to check for consistency of treatment effect for type of consent (written versus verbal).

In addition to the main primary outcome model, a further adjusted model will be fitted to control for any baseline imbalances of key variables between the groups.

